### Prioritising attributes and determining choice sets

Attributes and levels identified in phase 1 across all the interviews will be finalised by the study team based on the discussion transcripts. To ensure that the final set of attributes and levels represents a pragmatic and desirable set, they will be further vetted with external stakeholders such as ministry representatives and NGO leaders working in the CHW space. Efforts will be made to have clear definitions of each attributes and avoid conceptual overlaps across attributes and levels.

A fractional factorial design, which only takes a subset of choice sets, will be generated as too many choice sets place cognitive burden on respondents.^29^ An orthogonal design will be generated using Sawtooth Software Inc (Sequim, Washington, USA),^53^ where each attribute will be independent of each other and each attribute level will occur equally often (balanced).^35^

Sawtooth Software Inc. To generate the experiment will be unlabelled, full profiles and consist of three alternatives, that is, two job alternatives and an opt-out option.

The DCE questionnaire will include questions about respondent demographics, content and years of training as a CHW, socioeconomic status, and current level and quality of supervision. The order of the choice sets will be randomised to avoid positional bias. In each questionnaire, a dominant alternative will be included where one job option is superior to the other on all characteristics so that internal consistency and rationality of the responses can be considered during analysis.^29^ Finally, the questionnaires will be pretested with a subset of 20–30 respondents and changes made to the content and wording of the questions to account for any conceptual overlap and lack of clarity.

### Phase 2: sampling and approach for the DCE

In each country, the questionnaire will be translated into local language(s). The survey will be administered face-to-face to the CHWs by trained data collectors on tablets using the Open Data Kit software.^54^ First, the purpose of the study will be explained. The data collectors will explain the meaning of each attribute to the CHWs to support comprehension of the choice tasks. Each CHW will consider a set of job alternative and will be asked to choose an option they prefer. They will also have to option to opt-out that is, choose neither of the job alternative presented to them.

Sample size calculation in DCE studies mostly rely on rule-of-thumb estimates.^51^ For estimation of a DCE model, Lancsar and Louviere^30^ suggested that if respondents receive the same design, one rarely requires more than a sample size of 20 respondents. Other studies have shown that sample sizes of 40–100 respondents or up to 300 respondents may be adequate for reliable statistical analysis.^55^ The sample size calculation for this study is guided by the rule-of-thumb approach proposed by Johnson and Orme, as well as expected number of choice sets and pragmatic considerations around time and budget to conduct the study across the four countries.^56 57^ This approach was selected as it provides a better method of sample size calculation over other techniques such as those proposed by Lancsar and Louviere. According to Johnson and Orme, the minimum sample size *N* needed to detect differences in the preferences is dependent on the number of analysis cells *c,* number of choice sets *t* and number of alternatives *a* as shown in the following equation:

N§amp;gt;500c/(t×a)

Assuming a main effects model, then *c* will be equal to the largest number of levels for any of the attributes.

If we assume that respondents will face a maximum of 18 choice sets, the largest number of levels of any attribute in a main effects model is four, and that each task has two alternatives (excluding the opt-out), then using the above equation, we derive a minimum sample size of 56. Therefore, we estimate that recruiting a minimum of 150 CHWs per cadre per country to be more than sufficient to detect differences in preferences. A total of approximately 900 respondents across the four countries will be recruited for phase 2 (Bangladesh 300; Haiti 150; Kenya 150; Uganda 300). Based on the total sample size, an equal number of CHWs will be recruited per geographic area in discussion with the county/district health management teams to get broad representation of the types of CHWs.

### Public and patient involvement

Phase 1 of the study is structured to formally gather feedback from the broader community that supports CHWs, including national and international stakeholders and donors, other health officials, CHW supervisors and CHWs themselves. Opinions and experiences of these stakeholders are critical to shaping the questionnaire design and approach for the phase 2 of the study. Health officials at the facilities will be involved in the identification and recruitment of the CHWs in phase 2 of the study. Study results will be disseminated through in-country workshops where health officials involved during the design and recruitment phase will be invited to participate.

### Analysis plan

Conditional logit model will be used as the base model as it is congruous with RUT.^33^ This will model the probability of choosing one job alternative over another given the differences in the attribute levels. Preference heterogeneity will be explored by introducing interactions between the attributes. Furthermore, the relative importance CHWs place on the job attributes will be quantified. Additionally, where feasible, marginal WTA estimates will be computed which is the amount of money CHWs are willing to accept to compensate for the worsening or improvement of an attribute.^35^ The monetary attribute will be monthly salary while for volunteer CHWs, it will be stipends.

However, one of the shortcomings of the conditional logit model is that the assumption of the independence of irrelevant alternatives (IIAs) must hold. This is as a result of the error terms being assumed to be independently and identically distributed following extreme value type 1 (Gumbel) distribution. To relax IIA and further explore preference heterogeneity, a MMNL model will be used. MMNL presumes that some or all the parameters are randomly distributed with a particular probability distribution.^33^ MMNL will result in means which represent the choice probabilities and SD which denote heterogeneity. Stata 16 software will be used in the analysis.^58^

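### Interactions between attributes cannot show that preferences differ between CHWs, and no stated analysis links preferences to the respondent characteristics collected

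*Protocol article*

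**What the plan says.** Under Analysis plan, the protocol article makes the conditional logit the base model and states: "Preference heterogeneity will be explored by introducing interactions between the attributes". The next paragraph adds a second approach: "To relax IIA and further explore preference heterogeneity, a MMNL model will be used". The standard deviations of the random parameters are to be read as heterogeneity.

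Three other places bear on this:

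- **Data collected** (Prioritising attributes and determining choice sets): "The DCE questionnaire will include questions about respondent demographics, content and years of training as a CHW, socioeconomic status, and current level and quality of"; the list closes with supervision.
- **Design** (same section): "A fractional factorial design, which only takes a subset of choice sets, will be generated". It is described as orthogonal and level-balanced. Its resolution, the number of versions and the number of attributes are not given.
- **Sample size** (Phase 2: sampling and approach for the DCE): "Assuming a main effects model, then *c* will be equal to the largest number of levels for any of the attributes".

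The limitations section expects preferences to vary with the CHW's organisation and past experience in the role. The introduction, setting out the theory, says that utility depends partly on who is choosing.

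**The concern.** The article names a method for a purpose that the method cannot serve. An interaction between two job attributes tests whether utility is additive, for example whether training is valued more when pay is higher. It does not compare one CHW with another. An analyst who follows the sentence would fit the wrong terms under the heading of heterogeneity. A null result could then be taken as uniform preferences, and a clear one as varied preferences; neither follows.

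At stake is the question of which CHWs value which incentive. That matters to policy-makers choosing packages, and the limitations section itself expects such differences. The questionnaire collects much of what is needed, but the analysis as stated does not use it.

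**Working it through.** **1. What each model can show.** Let n index CHWs, j jobs, x attributes and z a respondent characteristic.

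- Conditional logit with interactions between attributes: V(n,j) = Σ β_k x_jk + Σ γ_kl x_jk x_jl. No coefficient carries the index n. Two CHWs shown the same choice set get the same predicted probabilities whatever the γ are, so γ holds no information on differences between CHWs.
- Conditional logit with attribute-by-characteristic terms: the weight on attribute k becomes β_k + δ_k z_n. Here δ measures how preferences differ with z (observed heterogeneity).
- MMNL: the weight becomes β_k + σ_k η_nk, with η random. A σ_k above zero says that preferences vary. Without z in the model, it does not say with what they vary.

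The article states the first and third models. The second is not stated.

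**2. The plan's own sample-size figure.** The rule is N > 500c/(t×a), with c = 4 (largest number of levels), t = 18 (maximum number of choice sets) and a = 2 (alternatives without the opt-out), all from the Phase 2 section: 500×4/(18×2) = 2000/36 = 55.6, so 56. This agrees with the article. It covers main effects only.

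**3. The same rule extended to interactions.** Assumption: c becomes the product of the levels of the two attributes. The article defines c only for main effects.

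| Interaction | c | t = 18 | t = 12 |
|---|---|---|---|
| 4×2 | 8 | 4000/36 = 111.1, so 112 | 4000/24 = 166.7, so 167 |
| 4×3 | 12 | 6000/36 = 166.7, so 167 | 6000/24 = 250 |
| 4×4 | 16 | 8000/36 = 222.2, so 223 | 8000/24 = 333.3, so 334 |

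At t = 18, 150 respondents support c up to 150×36/500 = 10.8. Where two cadres in a country are pooled (300 in Bangladesh or Uganda), the limit is 300×36/500 = 21.6. So at 18 choice sets the 4×3 and 4×4 cases exceed a single cadre but not two pooled ones. The column for t = 12 shows the effect of fewer choice sets, since 18 is a maximum.

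**4. Can the design estimate all two-way terms?** One version of 18 sets with two jobs and an opt-out gives at most 18×2 = 36 independent contrasts. The layouts below are assumed, because attributes and levels are fixed only after phase 1. Ranks come from level-balanced random designs, evaluated at zero coefficients.

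| Assumed levels | Parameters (constant + main + two-way) | Rank, 1 version | Rank, 2 versions | Rank, 5 versions |
|---|---|---|---|---|
| six attributes of 3 | 1 + 12 + 60 = 73 | 36 | 69 | 73 (full) |
| 4,3,3,2,2,2 | 1 + 10 + 40 = 51 | 33 | 51 (full) | 51 (full) |
| six attributes of 2 | 1 + 6 + 15 = 22 | 22 (full) | 22 (full) | 22 (full) |

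Main effects alone were estimable in every case. A structured orthogonal plan may alias more than these random designs. The answer therefore depends on choices that the article does not report.

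**The case against.** A reader might infer that the design cannot estimate interactions between attributes at all, or that they are aliased with main effects. The documents do not support that. The article nowhere calls the design main-effects only; that phrase belongs to the sample-size rule. The number of attributes, the resolution and the number of versions are open, and several assumed layouts above estimate every two-way term. Nor does the plan say that all of them would be fitted. What stands is narrower: orthogonality and balance of the single attributes do not by themselves secure interactions, and the sample size was not argued for them.

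A reader might also infer that the plan has no valid heterogeneity analysis, or could say nothing about kinds of CHW. That too goes too far. The MMNL is a proper tool for unobserved heterogeneity, and its standard deviations would stand beside any interaction result, which lessens the risk of misreading. Attributes are set by country and recruitment is by cadre, so comparisons on those lines remain possible, although the Analysis plan does not state them.

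It is also fair to say that the sentence may be a slip, since the theory in the introduction points to respondent characteristics; that a full covariate list can be left to an analysis plan; and that interactions between attributes answer a legitimate question. None of this rescues the sentence. It is not a missing detail but a stated method that does not fit its stated aim.

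**Conclusion.** Wrong as written; should-fix. That interactions between attributes cannot show differences between CHWs follows from the form of the conditional logit and holds whatever design is generated. The MMNL mitigates this but does not cure it, because it does not say which CHWs differ.

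The effect is limited. The step is exploratory, and the error does not in itself alter the main-effect preferences, the relative importance of attributes, the willingness-to-accept estimates or the MMNL.

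The secondary point is that support for interactions between attributes is not shown, rather than shown to be absent. The figures of 167 and 223 against 150 rest on the assumed extension of the rule of thumb. The rank results rest on assumed layouts and on fitting all two-way terms.

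**What to change.** Replace the sentence in the Analysis plan with: *Observed preference heterogeneity will be explored by interacting the attributes with pre-listed respondent characteristics already collected (for example demographics, training, socioeconomic status, supervision, and cadre where pooled); unobserved heterogeneity will be explored with the MMNL.*

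If interactions between attributes are also of interest, describe them as tests of complementarity between incentives and name the few that matter. Then generate the design so that they are estimable, and check the number of respondents for those terms.

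The first change costs one sentence and needs no new data or respondents, since these covariates are already in the questionnaire. The second needs a decision before the choice sets are generated. It may call for more than one design version or, for the larger interactions, pooling of cadres or a larger sample.

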### Limitations of the study in this context

Intrinsic and extrinsic factors influencing CHW incentive preferences are diverse and real-life decisions change over time; therefore, the relative importance of job preferences may vary with time and this needs to be considered when designing CHW programmes and policy interventions. We also recognise that CHW preferences can be different based on their organisational affiliations and prior experiences working as CHWs. While the study aims to capture a sample of CHWs across few areas in each country, the sample is not nationally representative of the preferences of all CHWs. We recognise that a comprehensive job package for CHWs may comprise many more factors that can be adequately captured by this study design. Finally, the results of this study will constitute stated preferences, reflecting responses to hypothetical scenarios. Decision makers will need to consider information from DCEs on CHW as part of the inputs to improved CHW performance and retention while making policies.

## Ethics and dissemination

This study has been reviewed and approved by the Population Council’s Institutional Review Board (IRB) in New York, the AMREF-Health Africa Ethics and Scientific Review Committee in Kenya, Zanmi Lasante’s IRB (Haiti) and the Higher Degrees Research Ethics Committee at Makerere University College of Health Sciences in Uganda, and the Bangladesh Medical Research Council. Dissemination activities will include sharing of findings through policy briefs, workshops, online blogs in community fora and peer-reviewed journal articles. The research approach is inherently designed around the need for research uptake by policy-makers. Involvement in the research from the beginning is the overarching strategy for promoting research uptake. To ensure there is significant demand for the final study findings, we will debrief policy-makers and other health system stakeholders at pivotal points in the initial stages as well as at the end of the study. We will share non-technical summaries of research results with all the partners for dissemination including the study’s key partners in the MoH. If there is enough interest, appropriate dissemination will be conducted with policy-makers in half-day workshops and to facilitate translation of the research findings in national CHW agenda.
